#### HAPA constructs (all assessments)

To assess the HAPA constructs, the following measures will be used, based on published guidelines and existing measures [37, 80, 81], as well as studies conducted on physical activity and exercise, particularly among women [64, 65, 68], adapting their content to postmenopausal women.

At baseline, the HAPA constructs of the motivational phase will be measured as indicators of the motivation for exercise and predictors of the creation of an intention to engage in a healthy and active lifestyle. The following constructs will be evaluated:

Absolute (personal risk) and relative (compared to an “average” woman of the same age and health condition who has transitioned the menopause) risk perceptions. Each perception will be assessed using five items that include the main physical and psychological manifestations of menopause and ageing processes (e.g., hot flushes and night sweats, sleep disturbances, low mood, mental slowness). Some items will also address conditions related to an active lifestyle (e.g., fatigue, weight gain, body image, severe health conditions). The statements are based on current evidence on health risks linked to menopause and the ageing process [82]. Participants will respond on a scale ranging from 1 (very unlikely) to 7 (very likely), and average scores will be calculated to obtain subtotal and total scores.Outcome expectations of adhering to regular exercise. These will be assessed with 15 items, 12 of which assess positive outcomes — i.e., expected benefits — including three main types of outcomes: 1) personal enjoyment and well-being (e.g., “I will feel better afterwards”, “I will feel satisfied with myself and proud of myself”), 2) management of menopause- and ageing-related changes and health (e.g., “I will manage better the changes and manifestations of my menopause”, “My quality of life will improve”) and 3) social recognition and support (e.g., “Other people will appreciate my willpower”, “I will be appreciated by others for that”), thus incorporating both intrinsic and extrinsic motivational regulations [83] that can drive exercise behaviour among middle-aged and older women [84, 85]. Negative outcomes — i.e., problems and difficulties derived from exercise — will be assessed with three items including feelings of discomfort resulting from doing something the participant does not like, time organisation difficulties and family financial challenges due to spending money on training and equipment (e.g., “It will be a burden on my financial situation”). Responses will range from 1 (not at all true) to 4 (completely true). Average scores will be calculated to obtain subtotal scores, and the difference between these scores will serve as an indicator of the balance between positive and negative outcomes, with positive scores suggesting a higher presence of benefits compared to costs.Action (task) self-efficacy. This assessment will include two components: a) Four items will assess motivational self-efficacy, which refers to an individual’s belief in their ability to adopt an active lifestyle, be physically active in daily life and engage in regular exercise at the minimum and optimal recommended levels (e.g., “I’m confident in myself for… doing vigorous-intensity exercise at least 3 times a week for 30 min or more”). b) Four items will assess preactional or task self-efficacy, which relates to an individual’s belief in their ability to overcome barriers and difficulties when immediately starting regular exercise (e.g., “I’m sure I can start exercising immediately… even if I have to reconsider my views on exercise”). Participants will respond on a scale ranging from 1 (not at all true) to 4 (completely true). Average scores are calculated to obtain subtotals for each component and a total score.Intention. Behavioural intentions for the following weeks will be assessed using a multi-habit measure consisting of 14 items. These items will correspond to various aspects of adopting a healthy lifestyle, such as improving/adopting healthy behaviours (e.g., healthy eating and weight control, emotional regulation, family and social relationships, sleep, leisure) and reducing/quitting unhealthy habits (e.g., tobacco or alcohol use), menopause-related health management (e.g., taking proactive steps for personal health, commitment to medical examinations), as well as increasing daily physical activity (1 item) and engaging in regular exercise at minimum (1 item) and optimal levels (1 item) (e.g., “I intend to… do at least 150 min per week of at least moderate intensity exercise”). Participants can respond on a scale ranging from 1 (don’t intend to at all) to 7 (strongly intend to). Average scores will be calculated to obtain a total score for 1) intention to adopt a healthy lifestyle, 2) intention to adopt an active lifestyle and 3) intention to engage in regular exercise at the optimal recommended levels.

In the post-intervention and follow-up phases, the HAPA constructs of the volitional phase will be measured as predictors of the translation of the intention into action, both at the initial adoption of the active behaviour and the medium- and long-term adherence to such behaviour. These constructs will be:

Outcome perceptions. These refer to an individual’s perceptions of the actual results achieved by engaging in exercise and will be assessed with the same measure used for assessing outcomes expectations at baseline. However, the wording of the items will be modified to assess perceived outcomes (e.g., “I have felt better afterwards”). The same indicators as those used for the baseline measure will be obtained for this assessment.Action planning for autonomous regular exercise. Action planning refers to the development of specific, organised behavioural plans for exercising after the intervention. It will be assessed using five items asking about the details of the exercise plans, including what, how, when, where, how often and with whom the exercise will take place once the supervised programme has finished (e.g., “I already have a structured plan detailing… the duration, intensity and frequency of my exercise routine”). Participants will respond on a scale ranging from 1 (not at all true) to 4 (completely true). An average score will be calculated based on these responses.Coping planning for maintaining regular exercise. Coping planning involves developing specific and organised behavioural plans to manage obstacles and setbacks. It will be assessed using five items asking about the specific strategies that participants have in place to overcome challenges such as interference with daily/weekly training plans, missing training sessions temporarily, staying committed to their exercise intentions when facing difficulties, remaining dedicated to exercise and being vigilant about situations that could lead to lapses and relapses (e.g., “I already have a structured plan detailing… what to do if I miss one training session”). Participants will respond on a scale ranging from 1 (not at all true) to 4 (completely true). An average score will be calculated based on these responses.Maintenance or coping self-efficacy for regular exercise. It will be assessed with 11 items that address the main obstacles middle-aged women can typically encounter when engaging in regular exercise. These obstacles include difficulties in creating the exercise habit (requiring multiple attempts or taking a long time to generate the habit), not experiencing immediate improvements in health and well-being, low mood, tiredness, lack of social support or having a partner or family members with a sedentary lifestyle (e.g., “I have confidence in myself to…stick to my exercise routine even if I don’t experience an immediate improvement in my menopause symptoms”). Participants will respond on a scale ranging between 1 (not at all true) and 4 (completely true). An average score will be calculated based on these responses.Recovery self-efficacy for managing lapses and relapses. It will be assessed with 14 items that address the main barriers middle-aged women are likely to encounter when re-engaging in exercise. These barriers include anticipating and managing difficulties in maintaining the habit (e.g., postponed plans), not feeling mentally prepared or motivated, not experiencing improvements in well-being or menopausal symptoms, being in low mood, feeling tired, lacking social support or having a partner with a sedentary lifestyle (e.g., “I am sure I can resume my exercise routine even if… I have already taken a break for several weeks”). The participants’ responses will range between 1 (not at all true) and 4 (completely true). An average score will be calculated based on these responses.Behavioural intentions for the subsequent weeks/months will be assessed at post-intervention and follow-up phases with the same measure as that used in the baseline phase. The same indicators will be obtained.

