To test the HAPA tenets in middle-aged postmenopausal women while filling the abovementioned gaps in the literature, the main aim of this study is two-fold. First, we aim to explore the influence of the social-cognitive variables relevant at each stage of the process of behavioural change based on HAPA predictions, and second, to test the goodness of fit of the model for exercise behaviour among women in early postmenopause (up to ten years after menopause). Specifically, the sub-aims of the present study protocol are the following:To explore the HAPA constructs at every stage of the change process in new exercisers, that is participants adhering to exercise practice while simultaneously receiving an intervention based on the HAPA model (Intervention group). These will be compared with regularly active (active control) and non-active (sedentary control) postmenopausal women, all with different socio-demographic, personal and clinical characteristics. Consequently, this sub-aim has the following specific objectives:to determine changes in the HAPA variables in the intervention group throughout the study phases, and in this regard:H1: we hypothesise that there will be a significant improvement in both intentional-motivational and postintentional-volitional variables in the participants in the exercise programme supplemented with the HAPA intervention.to compare the intervention, sedentary and active groups across the motivational and volitional phases of the HAPA model, and in this regard:H2: we hypothesise that, at baseline, non-active women (i.e., sedentary and intervention groups) will show similar HAPA determinants of exercise intention, while the active controls will obtain more positive results in the HAPA motivational constructs, andH3: we hypothesise that, at post-intervention and subsequent follow-ups, the new exercisers and the active women will show similar HAPA self-regulatory skills of the volitional-actional stage but will differ significantly from the sedentary women.To explore whether the HAPA constructs at the different stages of the process of behavioural change — i.e., non-intention, intention, action and disengagement — and phases of the process, that is, motivational (preintention) and volitional (intention-action-adherence), predict the adoption of exercise behaviour among postmenopausal women. In this regard:H4: we hypothesise that while the HAPA model will be applicable to this population, supporting its main predictions, adjustments in the model predictions will be necessary to optimise its explanatory power, considering the experiences, resources and opportunities of middle-aged women, andH5: personal (i.e., fitness status, physical and mental health status and sociodemographic variables) and clinical factors (i.e., menopausal manifestations and menopause-related quality of life) will intersect with HAPA variables in the prediction of exercise behaviour and behaviour change, supporting the existence of phenomena that are pertinent and exclusive of middle-aged women and are grounded in their experiences, realities and needs.

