To address the first research question, exercise behaviour and HAPA constructs of the motivational and volitional phases (primary outcomes) will be compared across different phases (baseline, post-intervention and follow-ups) (H1) and between the different study groups (intervention participants, sedentary controls, active controls) (H2 and H3). Within-group and between-group analyses will be conducted using parametric (e.g., 1-way or 2-way ANOVAs, Student *t* test) or non-parametric tests (e.g., Friedman’s *χ*^*2*^ test and Wilcoxon’s *Z* pair comparisons for related samples, Kruskal–Wallis’ *H* test and Mann–Whitney’s *U* pair comparisons for independent samples). The choice of test will be determined by the compliance with parametric assumptions of normality and homoscedasticity. A calculation of the effect size will be also conducted (e.g., Cohen’s d). Covariates (e.g., age, menopausal symptom burden) will be introduced (e.g., ANCOVAs).

The second research question (H4 and H5) will be addressed using analyses of bivariate associations (e.g., Pearson *r*, Spearman *rho*), multiple linear regression analyses and multilevel clustering analyses to explore the correlates and predictors of outcome variables as well as intraindividual profiles or patterns of associations. Path analyses and analyses of indirect relationships between variables (e.g., mediation, moderation) will allow for a deep understanding of the complex associations between the study variables. Structural equation modelling will allow for testing the fit of data to the model based on HAPA predictions. Covariates will be introduced to control for their confounding effects (e.g., perceived health status). 

In addition, psychometric properties of the measures will be analysed (e.g., Cronbach’s *alpha*, intercorrelations).

A significance level of *p* < 0.05 will be established.

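### H1 calls for improvement from baseline in all HAPA constructs, but as described six of the eight, including all four volitional scales, are measured on only one side of the intervention

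*Protocol article*

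**What the plan says.** The first specific objective, in the section on aims and hypotheses, is "to determine changes in the HAPA variables in the intervention group throughout the study phases". H1 under it expects that "there will be a significant improvement in both intentional-motivational and postintentional-volitional variables in the participants in the exercise programme". Data management and analyses names exercise behaviour and the HAPA constructs of both phases as primary outcomes and says that they "will be compared across different phases (baseline, post-intervention and follow-ups) (H1").

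The Measures subsection on these constructs is headed "HAPA constructs (all assessments"), but its text divides the battery by phase. First: "At baseline, the HAPA constructs of the motivational phase will be measured as indicators of the motivation for exercise". The list that follows is risk perceptions, outcome expectations, action self-efficacy and intention. Then: "In the post-intervention and follow-up phases, the HAPA constructs of the volitional phase will be measured as predictors". That list is outcome perceptions, action planning, coping planning, maintenance self-efficacy, recovery self-efficacy and intention.

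Two entries link the lists. Intention is stated to be reassessed later with the baseline measure. Outcome perceptions reuse the outcome-expectation items, but "the wording of the items will be modified to assess perceived outcomes".

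**The concern.** H1 is a within-group statement about change from the pre-intervention level, so each construct needs a value before and a value after, on the same scale. The construct lists give that pair for intention alone.

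The gap falls on what the intervention is meant to change. According to the Intervention section, the first two sessions address risk perceptions, outcome expectations and action self-efficacy. Risk perception and action self-efficacy are not listed for remeasurement. Later sessions teach action planning, maintenance and coping self-efficacy and relapse management, and the scales for these are first described after the teaching is over.

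If the study runs as described, post-intervention levels, or changes between follow-ups, could be reported as the improvement H1 predicts, on outcomes declared primary. The randomised comparison of the volitional scales also has no own-baseline covariate, and the planned mediation models have no baseline value of those mediators. An analysis plan written later cannot recover a baseline that was never collected.

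**Working it through.** The plan states no figure on this point, so the check is a count of constructs and items from the Measures subsection on HAPA constructs.

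**Constructs, with outcome expectations and outcome perceptions counted as one**

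| Construct | Items | Baseline | Post-intervention and follow-ups |
|---|---|---|---|
| Risk perception (absolute, relative) | 5 + 5 = 10 | yes | not listed |
| Action self-efficacy (two components) | 4 + 4 = 8 | yes | not listed |
| Outcome expectations / perceptions | 15 | yes, as expectations | yes, reworded as perceptions |
| Intention | 14 | yes | yes, same measure |
| Action planning | 5 | not listed | yes |
| Coping planning | 5 | not listed | yes |
| Maintenance self-efficacy | 11 | not listed | yes |
| Recovery self-efficacy | 14 | not listed | yes |

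**Count**

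- Constructs in total: 4 at baseline + 6 later − 2 on both lists = 8.
- On one side of the intervention only: 2 (risk perception, action self-efficacy) + 4 (volitional scales) = 6.
- On both sides but reworded: 1. The example item moves from what the woman expects to feel to what she has felt. A difference score can be computed, but it sets expected against perceived results.
- On both sides with the same measure: 1 (intention).
- No like-for-like pair: 6 + 1 = 7 of 8. If the reworded outcome scale is accepted as the same construct, 6 of 8. For the four volitional scales, 4 of 4 lack a baseline under either count.

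**Against each hypothesis**

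- H2 compares motivational constructs between groups at baseline. The described schedule supports it.
- H3 compares volitional constructs between groups from post-intervention onwards. The described schedule supports it.
- H1 needs both sets before and after. The described schedule does not support it.

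**Items needed to close the gap**

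- At baseline: 5 + 5 + 11 + 14 = 35. The HAPA battery goes from 10 + 8 + 15 + 14 = 47 to 47 + 35 = 82 items.
- At later assessments: 10 + 8 = 18, plus the 15 original outcome-expectation items. The battery goes from 15 + 5 + 5 + 11 + 14 + 14 = 64 to 64 + 18 + 15 = 97 items.

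No sample-size figure depends on this.

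**The case against.** The strongest reply is that the word only is an inference. No sentence says that a construct is measured solely at baseline or solely afterwards. The subsection heading, the objective above H1 and the analysis section all point to measurement throughout, and Figure 2, which the text says gives the time points of every measure, cannot be seen here. This stands as a reason for care about what will actually be done. It does not remove the problem. The construct lists are the most specific text on timing, and the remark that intention is repeated with the same measure would be needless if everything were repeated. If Figure 2 shows the full battery at each assessment, it contradicts the construct lists; if it shows the split, H1 cannot be tested as written.

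A second reply is that HAPA is a stage model, so different constructs matter at different stages. That justifies the schedule for H2 and H3, but H1 was written as improvement in both sets.

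A third is that the section on health and well-being lists expected benefits of exercise among measures taken at all assessments. That is a separate ad hoc questionnaire. It covers none of the volitional scales and is not the 15-item HAPA scale.

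Three stronger readings are tempting, and the documents do not support them.

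- A reader might infer that the volitional half of H1 leaves nothing to estimate. The volitional scales are described at post-intervention and at 1, 3, 6 and 12 months, so change after the intervention is estimable. The intervention and sedentary groups are randomised, so their post-intervention difference does not need a baseline to be a fair comparison; the missing baseline mainly costs precision.
- A reader might infer that later change can show only retention or decay. The intervention aims at a shift to self-regulated exercise after the programme, so a further rise is possible.
- A reader might infer that the gap H3 predicts is produced by item wording, since the action-planning description refers to the time after the supervised programme. Only that description and a few example items are shown, and a woman without an exercise plan can truthfully give the lowest answer. The wording deserves attention; an artefact is not shown.

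**Conclusion.** The point holds in this form: as the constructs are described, the within-group improvement from baseline that H1 and its analysis specify cannot be tested for six of eight HAPA constructs, including all four planning and volitional self-efficacy scales. The figure is seven of eight if the reworded outcome scale is not accepted as the same construct. Only intention has a like-for-like pair.

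This assumes that the construct lists, and not the heading, give the true schedule. If the heading is right, the lists are wrong and need correction, so the document is inconsistent either way. H2, H3, the randomised contrasts at post-intervention and the analysis of exercise behaviour, whose questionnaire is set for all assessments, are not undermined. What is wrong is the match between H1 and the data described for it, and that matters because these constructs are declared primary.

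**What to change.** 1. Reconcile the subsection heading, the two construct lists, Figure 2, H1 and the analysis section so that they state one schedule.
2. Add action planning, coping planning, maintenance self-efficacy and recovery self-efficacy (35 items) at baseline. Word the action-planning items so that they do not presuppose the supervised programme, and use that wording in every group and at every assessment.
3. Add risk perception and action self-efficacy (18 items) and the 15 original outcome-expectation items at post-intervention and follow-ups. Report expectations and perceptions as separate constructs.
4. Where baseline has already been taken, restate H1 and its analysis. Claim baseline-to-post change only for constructs measured both times with the same wording. For the volitional constructs, make the test the randomised intervention-minus-sedentary difference at post-intervention, and report later within-group change as change after the intervention, not as improvement from baseline. The same between-arm test is available for action self-efficacy only if that scale is added at post-intervention.
5. Do not restrict outcome perceptions to exercising women in the randomised comparison. That would select on behaviour after randomisation, and it conflicts with the plan's commitment to keep non-adherent participants in the analyses.

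The cost is a longer online survey: 35 more items at baseline and 18 + 15 = 33 more at each later assessment. The documents give no completion time and already call the assessment exhaustive, so the burden should be weighed. Changing the schedule or H1 is also a protocol change, which the plan undertakes to report to the ethics board, the registry and in publications. If baseline collection is complete, the volitional baselines cannot be recovered and only the restatement remains for those four scales.

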### Measures

Measurements will be taken at baseline, post-intervention and at 1-, 3-, 6- and 12-month follow-ups. This comprehensive assessment will enable the exploration of the factors that predict the initiation and maintenance of exercise behaviour, as well as the stages of the behaviour change process. 

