### Intervention

A three-component intervention will be offered, which includes:

A multicomponent, supervised exercise programme with a 3-month (12 weeks) minimum duration will be offered to the intervention group. The exercise programme will consist of three 1-h weekly sessions on alternate days. Participants will be able to choose from several schedules available in both the morning and afternoon periods. The programme will be designed and implemented by experts in Exercise and Sport Sciences and Sport and Exercise Medicine, following international recommendations for exercise in middle-aged women [96, 97]. The programme will include training for aerobic cardiorespiratory fitness, muscle resistance, as well as other fitness functions including flexibility, coordination and balance. Hence, it will meet the required conditions in terms of activity type, duration, frequency and intensity parameters and principles and methodology of training for a healthy, safe, successful and enjoyable practice for adult women, thus being suited to their characteristics and needs for maximising benefits while minimising risks. The programme will be implemented in supervised group classes conducted in a gym facility (e.g., in the university campus). To assess adherence to the programme, objective tracking measures will be utilised, including attendance monitoring. All these features are designed to optimise participation as well as outcomes. Additionally, a health insurance policy will be put in place to cover any potential risks and provide necessary medical assistance if required.A simultaneous intervention focusing on self-management of behavioural change, based on the tenets of the HAPA model, will be offered throughout the duration of the exercise programme. This intervention has been designed based on previous HAPA-based interventions [98–103]. To summarise, the intervention will provide information on the benefits of an active lifestyle and exercise, specifically for postmenopausal women, addressing risk perceptions and outcome expectations while facilitating the creation of an intention (Session 1). The participants will be also educated on the key factors for adopting and maintaining an active behaviour, such as identifying barriers and facilitators, basic self-monitoring and self-management skills for action regulation (e.g., self-monitoring, self-reinforcement, setting a daily time schedule, emotional regulation, seeking social support and reinforcement from significant others); these elements contribute to improving motivational action self-efficacy (Session 2). The subsequent 3 to 5 sessions will focus on motivational determinants of exercise initiation, including goal setting (behavioural intention), action planning and pre-actional/task self-efficacy to improve motivation and action initiation. Sessions 6 to 9 will address volitional determinants of maintaining adherence, covering self-regulatory skills including action and maintenance plans for autonomous exercise, maintenance and coping self-efficacy and relapse management (i.e., risk identification, functional responses and coping skills training). A final session is devoted to summarising the personal progress of the participants with this intervention. The aim of this intervention is to ensure that women not only adhere to the supervised exercise programme offered within the study, but mainly to promote long-term, self-managed adherence to the newly established lifestyle beyond the completion of the supervised exercise programme. To achieve this, the adherence promotion intervention will be delivered during the entire implementation of the exercise programme, divided into two phases according to the process of behavioural change. During the first phase of the programme, the focus will be on addressing issues pertaining to initiation and short-term maintenance. Researchers and implementers will play a central role in providing external regulation and support as a strategy to facilitate adherence. During the second phase of the programme, the emphasis will shift toward long-term maintenance. Building on the knowledge and skills acquired by the participants, the intervention will promote the transition to self-regulation and the development of intrinsic motivation based on enjoyment and personal growth.

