In addition, there is a lack of previous research on the fit of the HAPA model for predicting active behaviour in early postmenopausal women [64, 65, 68]. In order to more thoroughly explore the influences of HAPA constructs on exercise behaviour adoption, longer interventions (i.e., exercise programme, HAPA-based intervention) and follow-ups would be necessary. Nevertheless, 3 to 4 months is considered to be sufficient to progress through the intention to action phases, while an additional 12-month period allows for the transition from initiation to the initial sustainability of habits, taking into account the natural fluctuations in behaviour [50, 124–128]. Evidence suggests that the main motivational and self-regulatory changes that improve adherence occur in the first 1–2 months of practice [129] and the first 6 to 12 months of adherence [130], respectively.

Finally, the type of methodology used in the design and data analysis (i.e., methodological and statistical control) will make it possible to overcome the limitations of the study design and its potential weaknesses. Nonetheless, further research will be needed to replicate our findings.

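### Volitional constructs are named as predictors of initial adoption but are first measured after the programme in which adoption takes place

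*Protocol article*

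**What the plan says.** All references are to the protocol article.

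- **Visits (Measures).** "Measurements will be taken at baseline, post-intervention and at 1-, 3-, 6- and 12-month follow-ups". No assessment falls inside the programme.
- **Baseline constructs (HAPA constructs).** "At baseline, the HAPA constructs of the motivational phase will be measured as indicators of the motivation for exercise". These are risk perceptions, outcome expectations, action self-efficacy and intention.
- **Later constructs (same section).** "In the post-intervention and follow-up phases, the HAPA constructs of the volitional phase will be measured as predictors". They "will be measured as predictors of the translation of the intention into action, both at the initial adoption of the active behaviour" and at the later stage of keeping it up. The list covers outcome perceptions, action planning, coping planning, maintenance self-efficacy and recovery self-efficacy. Intention is asked again.
- **Programme (Intervention).** The intervention group is offered a "supervised exercise programme with a 3-month (12 weeks) minimum duration". Its first phase deals with initiation and short-term maintenance, and the trainer records attendance.
- **Behaviour (Active behaviour).** The short IPAQ is given at every assessment and refers to the last seven days.
- **Analysis (Data management and analyses).** H4 and H5 are addressed with "multiple linear regression analyses and multilevel clustering analyses to explore the correlates and predictors of outcome variables", followed by path, mediation and structural equation models. No time order between predictor and outcome is stated.

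**The concern.** A prospective predictor has to be measured before the outcome it predicts. For the intervention group, the move from not exercising to exercising happens while the supervised programme runs. The constructs named as predictors of that move are not recorded until it is over. A later analysis plan cannot repair this, because the data would not exist.

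A related risk concerns the later visits. If a construct and the IPAQ from the same visit are put in one model, the reported week of exercise precedes the construct score. A woman who has exercised may for that reason report firmer plans and greater confidence. The expected HAPA pattern could then appear without any forward effect of the constructs. The same applies to the fitness, health and menopausal measures in H5. They are repeated at all visits, and exercise may itself change them. H4 and H5 concern prediction of the adoption of exercise, so the direction of the association is central to both.

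**Working it through.** No sample-size figure is at issue. The check sets out what is measured when.

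| Time | Volitional constructs | IPAQ (past seven days) |
|---|---|---|
| Baseline | no (motivational constructs and intention only) | yes |
| Programme, at least 12 weeks | no | no (attendance recorded) |
| Post-intervention | yes | yes |
| 1 month | yes | yes |
| 3 months | yes | yes |
| 6 months | yes | yes |
| 12 months | yes | yes |

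**Step 1: when adoption occurs.** Two places in the article date it. The Intervention section assigns initiation to the first phase of the programme. Strengths and limitations considers 3 to 4 months sufficient for the passage from intention to action and reserves the further 12 months for the start of sustained habit. Both place adoption at about the programme period.

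**Step 2: volitional measurements before or during adoption.** From the table, the count is 0.

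**Step 3: what the items ask.** The intervention treats action planning as a determinant of starting exercise (sessions 3 to 5). The measure, however, asks about plans for autonomous exercise once the supervised programme is over. Outcome perceptions ask what exercising has already brought, so by definition they follow the behaviour. Neither score could stand in for the state of mind before starting.

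**Step 4: same-visit pairs of volitional score and IPAQ.** There are 5 (post-intervention, 1, 3, 6 and 12 months). In all 5, the IPAQ week comes before the score.

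**Step 5: pairs in the correct order (score at one visit, IPAQ at the next).** There are 5 − 1 = 4: post-intervention to 1 month, 1 to 3 months, 3 to 6 months, and 6 to 12 months. All four concern exercise after the programme.

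**Step 6: what can predict adoption.** The baseline motivational constructs and intention precede the programme, and attendance is recorded during it. That pair is correctly ordered and already planned.

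**The case against.** **Another meaning of initial adoption.** It could mean autonomous exercise after the programme. The planning items refer to that period, and the intervention's main aim is said to be self-managed adherence afterwards. The post-intervention score would then precede the 1-month IPAQ. This reading is possible but less well supported. The article dates initiation to the first programme phase and separates initial adoption from medium- and long-term adherence. If the later meaning is intended, the text should say so.

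**All assessments.** The heading over the HAPA measures says they are taken at all assessments, and the timeline figure is not shown. But the text below the heading splits the constructs by phase, and H2 and H3 follow the same split.

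**Same-visit models.** A reader might infer that the plan pairs each score with the IPAQ from the same visit, so that H4 and H5 would be confirmed by reverse causation. The article does not say this. It calls the study longitudinal and prospective, and the lag of a model is commonly left to the analysis plan. What stands is a risk left open, which the design already allows the authors to close. Baseline constructs, fitness and symptoms do precede adoption, and H1 to H3 are not affected.

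**The early window.** A reader might also take the remark that "the main motivational and self-regulatory changes that improve adherence occur in the first 1–2 months of practice" as showing that volitional change falls between visits and needs a questionnaire during the programme. The sentence goes on to give 6 to 12 months as a second window and ends with the word respectively. The first window thus belongs to motivational changes and the second to self-regulatory ones, for which visits exist. The volitional items also suit neither the early programme weeks nor sedentary controls. This argument is not relied on.

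**Size of the bias.** The article gives no correlation between past exercise and later construct scores, so the amount of reverse causation cannot be stated.

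**Conclusion.** The article assigns the volitional constructs a role that its own schedule rules out. With no measurement before or during the programme, they cannot prospectively predict initial adoption in the intervention group. This rests on adoption taking place within the programme, which two sections of the article support.

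The second part is conditional. Any H4 or H5 model that used the five same-visit pairs would have behaviour preceding its predictor. The article neither commits to such models nor excludes them, and four correctly ordered pairs permit a proper test of later adherence. The point therefore concerns one misassigned predictor role and one time order worth fixing. It does not mean that the HAPA model cannot be tested. The correction is worth making because it serves the study's central aim and needs no new data.

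**What to change.** 1. **Restrict the stated role.** In the HAPA constructs section, let the volitional constructs predict exercise after the programme only. For adoption in the intervention group, use baseline motivational constructs and intention to predict the attendance already recorded.
2. **State the time order for H4 and H5.** Let constructs and time-varying health measures at visit k predict IPAQ at visit k+1, adjusted for IPAQ at visit k. Report same-visit associations as descriptive.

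Both are changes of wording and use data already planned. The price of the second is one visit pair per woman, four instead of five for the volitional constructs. The adjusted lag guards against current exercise driving the association. It does not remove unmeasured common causes, so the results should still be described as prospective associations.
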